### Primary outcome measure

The primary outcome measure is near FH-SDS (using the WHO Growth Charts [29]) and is considered a non-inferiority outcome. The groups will be compared using a linear regression model adjusting for the minimisation variables and baseline height SDS, to compare the mean near FH-SDS between the GH + and GH − group. The adjusted mean difference in near FH-SDS will be presented alongside a 95% confidence interval. Non-inferiority for the primary outcome will only be concluded if the lower bound of the 95% confidence interval limit is above − 0.55 for both the ITT and per-protocol analyses.

### Secondary outcome measures

Growth and bone-related secondary outcomes will be considered non-inferiority outcomes and so will be analysed as per the primary outcome using both ITT and per-protocol analyses. Biochemistry and adverse event outcomes will be considered superiority outcomes and so will be analysed using ITT analyses only. Continuous outcomes will be analysed using linear regression models, adjusting for minimisation variables and baseline response (where applicable). Adjusted mean differences will be presented alongside 95% confidence intervals. Binary outcomes will be analysed using log binomial regression models, adjusting for minimisation variables, with both a log and identity link to obtain risk ratios and risk differences, respectively. *P*-values will only be reported for superiority outcomes. The number of participants who experience an SAE will be reported alongside the number of SAEs reported.

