### Consent and recruitment

Children with I-GHD reversal under the care of a paediatric endocrinologist and/or a general paediatrician will be recruited from 12 UK and 5 Austrian centres. Administration of GH medication will be stopped for a minimum of 6 weeks prior to a GH re-test being performed in line with local protocols. If the patient is thought to be eligible after GH retesting, the clinical team will send the participant information sheet (PIS) to the patients’ parent/guardian, and they will be invited into clinic to discuss potential participation in the trial. It will be the responsibility of the principal investigator (PI) or their delegate to ensure written informed consent is obtained for each participant and/or parent/guardian prior to performing any trial-related procedures. The responsibility for obtaining consent may be delegated by the PI to another clinician as captured on the GHD Reversal Trial site signature and delegation log. If the potential participant and/or parent/guardian are willing to take part in the trial (and meet all of the eligibility criteria), they will be asked to sign and date the latest version of the GHD Reversal Trial informed consent form (ICF) and Assent Form if appropriate and the child will be randomised to one of the study arms. The participant and/or parent/guardian will give explicit consent for the regulatory authorities, members of the research team and or representatives of the sponsor to be given direct access to the participant’s medical records as required. This will be specified on the ICF.

We will request consent for review of participants’ medical records and for the collection of blood samples to assess serum IGF-1 and lipid profiles (fasting lipids − serum triglyceride and serum total cholesterol) and peak stimulated GH.

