#### Randomisation

Following confirmation of patient eligibility, receipt of informed consent and completion of all questions and data items on the randomisation form, the patient will be randomised at the level of the individual in a 1:1 ratio to either continue (GH +) or discontinue (GH −) growth hormone therapy. Randomisation will be provided by a secure online randomisation system at Birmingham Clinical Trials Unit (BCTU). A minimisation algorithm will be used within the online randomisation system to ensure balance in the treatment allocation over the following variables:Tanner stage (B2 (females) or 6– < 9 ml testicular volume of the largest testicle (males) vs B3 (females) or 9–12 ml testicular volume (males).Sex (male vs female).Participating centre.

Following randomisation, a confirmatory e-mail will be sent to the responsible clinician including the child’s trial number and treatment allocation.

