#### Sample size and power calculation

Determination of non-inferiority margin was carefully considered, following extensive consultation. A questionnaire was sent to all investigators, British Society for Paediatric Endocrinology and Diabetes clinical study group members, and a patient support group representative (*n* = 34), giving several options for ‘acceptable deficit’ in various FH outcomes. These FH outcome options for comparison between the GH + and GH − groups were (1) the percentage of children reaching normal adult height (0 ± 2SD), (2) the percentage of children reaching mid-parental TH (0 ± 2SD) and (3) the near FH (in SDS/cm). Near-FH standard deviation score (near FH-SDS) was selected as the primary outcome.

Whilst the percentage of children reaching mid-parental TH [26] was the most popular outcome amongst respondents, data were not available to inform a sample size calculation. However, all the above options to express FH will be analysed in this trial as secondary outcomes. Other secondary outcomes are HRQoL, lipid profile, cost-effectiveness, and the bone health index (assessing effect of GH + /GH − on bone accrual and bone age using BoneXpert software).

For the primary outcome measure of near FH-SDS with a non-inferiority design comparing means and assuming equal variance, a non-inferiority margin of 0.55 near FH-SDS, a one-sided test with alpha = 0.025 and 90% power, a group size of 57 (total *n* = 114) would be needed (calculated using the SSI procedure in Stata 13). This calculation was based on a near FH-SDS (SD) of − 1.6 (0.9) using data from a population-based registry for patients with idiopathic GHD treated with GH and completing the scheduled treatment [27]. The non-inferiority margin is based on clinical opinion. Additional observational studies gave consistent results. Using the LMS growth software, a 0.55 height SDS score (using British 1990 Growth Charts [28]) approximates to 3.8 cm for boys and 3.3 cm for girls at age 23. With 17% allowance for withdrawal and loss to follow-up, a total sample size of 138 is required.

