### Statistical analysis

A separate statistical analysis plan (SAP) has been produced which provides a more comprehensive description of the planned statistical analyses which is available from the corresponding author on request. The primary comparison groups will be composed of those treated with GH (25–35 μg/kg/day) versus those not treated with GH. Non-inferiority outcomes will be analysed using both intention-to-treat (ITT) (i.e. all participants will be analysed in the treatment group to which they were randomised, irrespective of compliance or other protocol deviation) and per-protocol analyses (i.e. those participants who are considered adherent to their allocated intervention, as defined in the SAP). This is because an ITT analysis alone may bias results in favour of non-inferiority. Superiority outcomes will be analysed using ITT analyses only. For all primary and secondary outcome measures, summary statistics and differences between groups will be presented with 95% confidence intervals. Outcomes will be adjusted for the minimisation variables and baseline values where appropriate. No adjustment for multiple comparisons will be made.

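### With 17 centres entered as fixed indicators, the log-link and identity-link models for binary outcomes will usually have no interior maximum, so their usual 95% confidence intervals would not be valid.

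*Protocol article*

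**What the plan says.** The Secondary outcome measures section of the protocol article sets the method for binary outcomes: "Binary outcomes will be analysed using log binomial regression models, adjusting for minimisation variables, with both a log and identity link". The log link is to give risk ratios and the identity link risk differences.

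The Randomisation section lists three minimisation variables: Tanner stage in two levels, sex, and "Participating centre". Under Consent and recruitment, children "will be recruited from 12 UK and 5 Austrian centres", which makes 17 centres.

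The general Statistical analysis section adds: "Outcomes will be adjusted for the minimisation variables and baseline values where appropriate". It promises 95% confidence intervals for all primary and secondary outcomes, and it refers to a fuller SAP, which is not shown here.

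The growth outcomes that are binary are the proportions reaching normal adult height and mid-parental target height. Both are treated as non-inferiority outcomes and are analysed in the ITT and per-protocol sets.

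**The concern.** A logistic model keeps every fitted risk between 0 and 1 automatically. Log-link and identity-link binomial models do not: the log link can exceed 1 and the identity link can leave the range at either end. When the data push a fitted risk to the limit, the maximum of the likelihood lies on the boundary. Software then often fails to converge, and standard errors based on an interior maximum no longer apply.

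A centre factor with about seven children per level invites this. If all children in one centre have the same outcome, the equations for that centre have no interior solution. Even without such a centre, one with a high success rate can be pushed to a risk of 1 for its most favourable combination of arm, sex and Tanner stage.

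What is at stake is the confidence interval. The article reports no p-values for non-inferiority outcomes, so these two proportions are judged on estimates and intervals alone. According to the sample size section, reaching mid-parental target height was also the outcome that survey respondents favoured most.

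**Working it through.** **Inputs.** From the article: 57 per arm (114 evaluable), 138 randomised, 17 centres, near FH-SDS mean -1.6 and SD 0.9. No event rate is given for either binary outcome. The rate for normal adult height is derived below; other rates are assumptions, shown as a range.

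**Reproducing the plan's sample size.** The article uses "a non-inferiority margin of 0.55 near FH-SDS" and "a one-sided test with alpha = 0.025 and 90% power".

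- n per arm = 2 × (1.960 + 1.282)² × 0.9² / 0.55² = 56.3, rounded up to 57, or 114 in total.
- 114 / (1 - 0.17) = 137.3, rounded up to 138.

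Both figures reproduce.

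**Children per centre.** 114 / 17 = 6.7, and 138 / 17 = 8.1 if nobody is lost.

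**Implied event rate.** Assuming normality, P(near FH-SDS > -2) = Φ((-1.6 + 2) / 0.9) = Φ(0.444) = 0.67.

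**Score equations for one centre indicator.**

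- Log link: Σ(y - p)/(1 - p) = 0. If every y = 1, each term equals 1 and the sum cannot be zero. If every y = 0, the sum approaches zero only as p goes to 0.
- Identity link: Σ(y - p)/[p(1 - p)] = 0. If every y is the same, all terms have the same sign and the sum cannot be zero.

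**How often a centre has successes only.** With 17 equal centres and rate 0.67:

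- 7 per centre: 1 - (1 - 0.67⁷)¹⁷ = 65%
- 8 per centre: 1 - (1 - 0.67⁸)¹⁷ = 51%

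**How often the full model has an interior maximum.** The simulated model had an intercept, arm, sex, Tanner stage and 16 centre indicators: 1 + 1 + 1 + 1 + 16 = 20 parameters. There was no treatment effect, and the centre SD on the logit scale was 0 or 0.3. The likelihood was maximised under the constraint 0 < p < 1, so software non-convergence is not counted as failure. There were 300 runs per scenario at 0.67 and 120 at the other rates in the table. Ranges cover the two centre SDs.

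| Rate | N | Centre sizes | Log link | Identity link |
|---|---|---|---|---|
| 0.50 | 114 | equal | 5-8% | 18% |
| 0.50 | 114 | unequal | 1% | 2-3% |
| 0.50 | 138 | equal | 17-21% | 47-50% |
| 0.50 | 138 | unequal | 0% | 3% |
| 0.67 | 114 | equal | 0-0.3% | 4-8% |
| 0.67 | 114 | unequal | 0% | 0-0.7% |
| 0.67 | 138 | equal | 0.7-1% | 9-13% |
| 0.67 | 138 | unequal | 0.3-0.7% | 0.7-1% |
| 0.80 and 0.95 | both | both | 0% | 0% |

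Monte Carlo error is about 1-2 percentage points at 0.67 and up to about 5 elsewhere.

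**Separating link from centre.** The same links with arm, sex and Tanner stage only:

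| Rate | Log link | Identity link |
|---|---|---|
| 0.67 | 98% | 99-100% |
| 0.80 | 88-95% | 93-98% |
| 0.90 | 42-64% | 47-69% |

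At the planning rate, then, the centre indicators cause the failure. At high rates the links are fragile even without centre.

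**The case against.** The strongest reply is that the article never says centre enters as fixed indicators. Its general section qualifies adjustment ("Outcomes will be adjusted for the minimisation variables and baseline values where appropriate"), and coding of centre and a fallback for non-convergence are normal SAP content. This stands in part. A random intercept or pooled centres would be compatible with the text, and the absence of a fallback from the article is not an error. But the sentence on binary outcomes carries no qualifier of its own, and the method it names fails on its plain reading. Dropping centre does not fully rescue it either, if the event rate is high.

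The second reply is that the link should not be blamed for what the centre indicators do. This stands at the planning rate. A logistic model with the same 16 indicators would also have infinite coefficients for single-outcome centres, so changing the link alone is no cure.

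A reader might infer three stronger things that the documents do not support:

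- **That the risk ratios and risk differences cannot be produced at all.** A boundary maximum can still give a point estimate. With an all-failure centre under the log link, only that centre's coefficient diverges, and the other centres still inform the treatment effect.
- **That analysts will have to pick a replacement after seeing the data.** A SAP already exists and may name a fallback, and no patients had been recruited at publication.
- **That the economic evaluation is compromised.** It uses attainment of target height, but the article describes estimating mean costs and outcomes by arm and does not say it takes them from these regressions.

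**Conclusion.** The point holds for the models as plainly written, with centre as fixed indicators. They will usually give no valid interior fit at rates of 67% or above. Results are better only near 50%, and there mainly when centres are equal in size: at best 21% of data sets for the log link and 50% for the identity link, with all 138 children analysed. What fails is the usual standard error and the promised interval.

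The conclusion rests on four assumptions:

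- Centre is coded as 16 indicators.
- Near FH-SDS is normally distributed, for the 67% figure.
- There is no treatment effect.
- Event rates other than 67% are assumed. The rate for target height is unknown; the article says it had no data on that outcome for a sample size calculation.

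A random centre effect was not simulated. The per-protocol set can be no larger than the ITT set, so the problem should not ease there. The primary analysis is a linear regression and is not affected. This is a correction worth making to secondary analyses, not a threat to the trial's main conclusion.

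**What to change.** In the Secondary outcome measures section, and in the SAP if it does not already do this, replace the two binomial models with one logistic regression on arm, sex and Tanner stage. Obtain both the risk ratio and the risk difference from it by marginal standardisation, with delta-method or bootstrap 95% confidence intervals. Modified Poisson regression with robust errors is an acceptable alternative for the risk ratio.

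Do not enter centre as 16 fixed indicators in the binary models. Use country (UK or Austria) or a random intercept for centre instead, and state which. Both changes are needed: the centre coding matters most at the planning rate, and the link matters if success rates are high.

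The cost is a sentence or two in the protocol and SAP, plus standard code. The small downside is less complete adjustment for centre, a minimisation factor, in these secondary analyses.

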### Subgroup analyses

Subgroup analyses will be limited to minimisation variables: sex and Tanner stage, for the primary outcome only. Tests for statistical heterogeneity (e.g. by including the treatment group by subgroup interaction parameter in the regression model) will be performed prior to any examination of effect estimate within subgroups. The results of subgroup analyses will be treated with caution and will be used for the purposes of hypothesis generation only.

### Missing data and sensitivity analyses

Every attempt will be made to collect full follow-up data on all trial participants; it is thus anticipated that missing data will be minimal. Participants with missing primary outcome data will not be included in the primary analysis in the first instance. This presents a risk of bias, and sensitivity analyses will be undertaken to assess the effect of any missing data. In brief, this will include a multiple imputation approach, using important variables to predict the near FH SDS and a last observation carried forward (LOCF) approach, which assumes no change from the previous assessment.

A further sensitivity analysis will be conducted to assess the impact of participants who have not reached near FH by the end of the study. For the primary analysis, all participants will be included and for any participants who have not reached near FH, their height recorded at the end of study follow-up visit will be used. Although we anticipate this to be a rare event, we will conduct a sensitivity analysis (for the primary outcome only) which excludes any participants who have not reached near FH by the end of the study. Full details are included in the SAP.

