### Study design

The study design is as follows: phase III, international, multicentre, open-label, randomised controlled non-inferiority trial, including an internal pilot study, qualitative sub-study and within-trial cost analysis. The duration of the trial will be 90 months, including a 12-month pilot phase.

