### Planned final analyses

The primary analysis for the trial will occur once all participants have either fulfilled the near FH definition (growth rate of < 2 cm/year and have reached a bone age of 14 years (females) or 16 years (males)), have completed the 36-month assessment or have withdrawn from the study or been lost to follow-up and corresponding outcome data have been entered onto the trial database and validated as being ready for analysis. All other outcome measure analyses will be undertaken when the final participant (as defined above) reaches their 36-month assessment.

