### Ethical considerations

In the UK, ethical approval, MHRA approval (Clinical Trial Authorisation), HRA approval and local capacity and capability assessments will be obtained prior to the start of recruitment. In Austria, CTIS ethical approval and BASG approvals (Clinical Trial Authorisation) has been obtained. The study will be conducted in accordance with the principles of GCP and comply with all legislation. This process will be managed by the BCTU trials management team in conjunction with UCL as sponsor (the sponsor played no part in the study design; collection, management, analysis and interpretation of data; writing of the report; and the decision to submit the report for publication). An independent DMC will ensure the safety and dignity of the study participants as well as the reliability of the results obtained. Information will be provided to parents and patients verbally and through parent and participant information sheets. The information sheets will clearly explain that participation in the trial is entirely voluntary with the option of withdrawing from the trial at any stage and that participation or non-participation will not affect the participant’s usual care which, for children who had ever been on GH would include monitoring to FH. Though all trials involving children require careful ethical consideration, we do not anticipate any specific ethical issues beyond those in randomised controlled trials within the paediatric population. There are no major concerns surrounding the withdrawal of GH in study patients with reversed I-GHD.

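### The primary analysis leaves out children with no obtained near-final height; if GH− leavers grow worse than stayers, both analyses in the decision rule lean towards non-inferiority, and routine-clinic heights could close much of the gap

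*Protocol article*

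**What the plan says.** Under Missing data and sensitivity analyses, the article states: "Participants with missing primary outcome data will not be included in the primary analysis in the first instance". It concedes that this may bias the result and plans multiple imputation and LOCF as sensitivity analyses. The same section promises to pursue complete follow-up for everyone and expects few missing values.

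Five other places bear on the point:

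- Statistical analysis defines ITT so that "all participants will be analysed in the treatment group to which they were randomised".
- Sample size and power calculation: "With 17% allowance for withdrawal and loss to follow-up, a total sample size of 138 is required".
- Primary outcome measure concludes non-inferiority only if the lower 95% confidence limit lies above −0.55 in both the ITT and the per-protocol analysis. The sensitivity analyses are not part of that rule.
- Planned final analyses starts the primary analysis once every child has reached near-final height, completed 36 months, or is recorded as one of those who "have withdrawn from the study or been lost to follow-up".
- On access to heights outside trial visits, Ethical considerations says that taking part or not leaves unchanged the "usual care which, for children who had ever been on GH would include monitoring to FH", and Consent and recruitment says: "We will request consent for review of participants’ medical records".

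**The concern.** The trial is a "phase III, international, multicentre, open-label, randomised controlled non-inferiority trial", so families know the allocation and can watch the child's growth. A family in GH− who sees poor growth has a plausible reason to leave. A family in GH+ is more likely to leave for reasons unrelated to height, such as the injections. If that happens, the GH− children who remain are taller on average than the GH− children who were randomised, and the estimated difference moves towards non-inferiority.

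Requiring both ITT and per-protocol to succeed does not protect against this, because a child with no height is absent from both. Standard multiple imputation assumes that exit is explained by data already recorded. LOCF assumes no change after the last visit and may hide a later fall-off in growth. Whatever these analyses show, the stated rule does not let them alter the conclusion.

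What makes this more than the usual missing-data caveat is the endpoint. It is a height, followed up in routine endocrine clinics, so for some leavers it may have been measured even though the trial has not collected it.

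**Working it through.** **Inputs from the article.** Margin 0.55, SD 0.9, one-sided alpha 0.025, power 90%, 57 per group, 17% allowance, total 138. Participants are "randomised at the level of the individual in a 1:1 ratio", hence 69 per arm.

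**The plan's own figure.** n per arm = 2 × (1.960 + 1.282)² × 0.9² / 0.55² = 56.3, so 57 per arm and 114 in total. Then 114 / 0.83 = 137.3, which gives 138 as an even total. The stated sample size reproduces. The allowance is 138 − 114 = 24 children, or 12 per arm.

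**Assumptions not in the documents.** The true difference is exactly −0.55. GH+ loss is unrelated to height. In GH−, a latent tendency to leave has correlation rho with near-final height SDS, and the 17% with the strongest tendency leave. Baseline height SDS, which the planned regression adjusts for, correlates 0.6 with near-final height SDS and is related to exit only through it.

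**Step 1: shift among stayers.** Losing a fraction f shifts the mean of the latent variable among stayers by h = φ(z_f)/(1 − f). For f = 0.17, z = −0.954 and h = 0.305. For f = 0.05, h = 0.109.

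**Step 2: bias and standard error.**
- Unadjusted: bias = rho × h × 0.9; SE = 0.9 × √(2/57) = 0.169.
- Adjusted for baseline: bias = rho × h × 0.9 × (1 − 0.6²); SE = 0.169 × √(1 − 0.6²) = 0.135.

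**Step 3: false non-inferiority** = Φ(bias/SE − 1.96).

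| 17% loss | rho 0 | rho 0.2 | rho 0.3 | rho 0.5 |
|---|---|---|---|---|
| Unadjusted bias (SDS) | 0 | 0.055 | 0.082 | 0.137 |
| Unadjusted rate | 2.5% | 5.1% | 7.1% | 12.6% |
| Adjusted bias (SDS) | 0 | 0.035 | 0.053 | 0.088 |
| Adjusted rate | 2.5% | 4.5% | 5.8% | 9.5% |

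A simulation of the baseline-adjusted model agreed with the last row to within about half a percentage point. The adjusted rows correspond to the planned analysis.

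**At 5% loss**, with 65.5 analysed per arm, the adjusted SE is 0.126 and the rates for rho 0.2, 0.3 and 0.5 are 3.1%, 3.5% and 4.4%.

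**If exit follows growth since baseline** rather than height itself, bias and SE both scale with the residual SD. For the same correlation, the rates then return to the unadjusted row.

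**Effect of retrieval.** With all 69 per arm observed, the missing-data bias is zero and power at the stated SD is 94.8% (unadjusted). Retrieval has its own cost. If the 17% had restarted GH and fully regained the deficit, the ITT difference would shrink by 0.17 × 0.55 = 0.094. With SE 0.9 × √(2/69) = 0.153 (unadjusted), a non-inferiority conclusion when full adherence would give −0.55 has probability Φ(0.094/0.153 − 1.96), about 9%.

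**The case against.** A reader might infer that every child who withdraws is dropped. The text does not say so: only a child whose primary outcome is missing is left out, and the article promises to pursue follow-up for all. A leaver whose height is obtained stays in.

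A reader might also infer that Planned final analyses closes the file on leavers. That section sets when the analysis may begin; it does not forbid retrieving a height first. Nor is it established that the trial can read leavers' records. Consent to record review is requested, but the article does not say that it survives withdrawal. A child lost to trial visits may be lost to the same clinic, and bone age, which is part of the near-final-height definition, may not be on file.

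The mechanism can be questioned too. A child may restart GH and remain in the ITT analysis. Heights are recorded every six months, so if families leave because of growth already seen, multiple imputation will repair part of the bias. The 17% is a planning allowance, not a forecast, and the actual loss may be smaller. Finally, withdrawal levels and retrieval procedures often sit in the full protocol, SAP or data management plan, none of which is shown.

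These points stand as limits on certainty and size. They do not remove the concern, because the complete-case rule and the decision rule are both stated in the article. Together they leave an acknowledged bias outside the conclusion, and the article does not connect record review with leavers' outcomes.

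**Conclusion.** The concern holds as a conditional one. The stated primary analysis is complete-case, it falls short of the article's own definition of ITT, and the planned sensitivity analyses cannot affect the non-inferiority conclusion. If exit from GH− is related to poor growth, the error favours the trial's hypothesis in both required analyses.

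Under the planned baseline-adjusted model, the size is about 0.03 to 0.09 SDS against a margin of 0.55. The one-sided error is about 4.5% to 9.5% instead of 2.5% at 17% loss, and about 3.5% (for rho 0.3) at 5% loss. These figures rest on an assumed rho, an assumed baseline correlation of 0.6, random loss in GH+ and a true difference at the margin. The documents supply none of these, and they do not show that the bias will occur or in which direction. The issue is worth correcting because the remedy is cheap; it does not invalidate the design.

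**What to change.** 1. In Missing data and sensitivity analyses, separate children who stop trial visits or allocated treatment from those who refuse further use of their data. For the first group, and for children lost to trial visits, retrieve routine-clinic heights, with dates and any GH restart, up to near-final height or 36 months. Analyse them in the randomised arm. Count as missing only children with no retrievable height or who refuse data use.
2. In Planned final analyses, require retrieval to be complete before the primary analysis starts.
3. Confirm in the consent wording that record review continues after a child stops visits unless the family objects.
4. For heights still missing, add a delta-adjusted (tipping-point) analysis and report it beside the primary result.

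The cost is some wording in the protocol, SAP and consent form, and a record request for up to about 24 children. According to Trial status, nobody had been recruited when the article was published.

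There are three downsides. Clinic heights are less standardised, so their source needs a flag. Bone age may be unavailable for some leavers. Heights after a GH restart can dilute the ITT difference, so restarts should also be flagged and reported by arm.
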